## Abstract

**Background:**

Evidence has been accumulating that it may be possible to achieve prevention in psychotic disorders. The aim of the Prevention Of Psychosis (POP) study is to reduce the annual incidence of psychotic disorders in a catchment area population through detection and intervention in the prodromal phase of disorder. Prodromal patients will be recruited through information campaigns modelled on the Scandinavian early Treatment and Intervention in Psychosis (TIPS) study and assessed by low-threshold detection teams.

**Methods/Design:**

The study will use a parallel control design comparing the incidence of first episode psychotic disorders between two Norwegian catchment areas with prodromal detection and treatment (Stavanger and Fonna) with two catchment areas without a prodromal intervention program (Bergen and Østfold). The primary aim of the current study is to test the effect of a Prodromal Detection and Treatment program at the health care systems level. The study will investigate: 1) If the combination of information campaigns and detection teams modelled will help in identifying individuals (age 13–65, fulfilling study inclusion criteria) at high risk of developing psychosis early, and 2) If a graded, multi-modal treatment program will reduce rates of conversion compared to the rates seen in follow-along assessments.

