Most patients experience a relative long period with non-psychotic symptoms before their first psychotic episode characterized by unspecific- and more specific symptom constellations (prodrome/Ultra High Risk (UHR) state). At the onset of psychosis, many have already experienced a loss of cognitive- and psychosocial functioning. We now know that individuals at high risk for psychotic disorders can be identified before this point of time. The present study builds on experiences from the Scandinavian Early Treatment and Intervention in Psychosis (TIPS) study [1,2], where the use of information campaigns and detection teams were instrumental in reducing the duration of untreated psychotic symptoms in the first episode. This reduction was followed by a more benign course of the disorder over ten years of treatment [3]. We here hypothesize that a similar program (Prodromal Detection and Treatment program - PDT) - aimed at identifying and treating help seeking individuals at high risk for developing psychotic disorders will a) significantly increase the number of high risk individuals that get in contact with the relevant services and b) that these individuals will be detected at a very early stage of illness development. After contact the high risk individuals will be allocated to a structured follow-along by a designated case manager or to a graded, multi-modal and primarily psychosocial treatment intervention. Patients will be offered active antipsychotic medication only at imminent risk of conversion to psychosis. We also hypothesize that the multi-modal treatment intervention will significantly reduce the number of persons converting to psychosis, and thus influence the incidence of new cases of first-episode psychosis. The study is designed as a regional multi-center study, involving central research- and clinical psychiatric organizations across the Health Vest region in Southern Norway, with significant international cooperation, and will involve all service levels from general practitioners to specialized psychiatric services. Two Norwegian treatment centers covering a population of 440 000 will collaborate in recruiting prodromal patients to the study: Stavanger and Fonna hospitals. The project organization has additional involvement from the research departments at Bergen University Hospitals and Sykehuset Østfold Hospital for establishing a first-episode psychosis incidence registration as another part of this research initiative. All study enrolled patients will be asked for blood samples and to be a part of the Norwegian NASATS program – Severe Mental Illness, aiming to identify new genetic variants associated with severe mental disorders [4].

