
### Rationale

Schizophrenia and other psychotic disorders are serious, costly, and disabling. They typically emerge in late adolescence and early adulthood, a critical phase of neurological, psychological and social development. Even if the number of new cases per year is low (varying between 15 in the TIPS study [1] to −30 per 100 000 per year [5], their early onsets combined with a high risk of chronic symptoms makes these into disorders with a high prevalence (1%).

Many patients display significant impairments already at start of first treatment, and it is known that course and outcome are poorer in patients that come late into treatment. Results from the TIPS study show for the first time that treatment can be initiated significantly earlier in psychotic disorders. This is in turn associated with less severe psychotic symptoms, suicidality and functional disabilities already at first treatment [1,6]. Follow-up after two- and five years in treatment demonstrate long-term advantages in the form of less severe negative symptoms, cognitive deficits, depressive symptoms and global dysfunction [7,8] and for the level of recovery rates up to ten year follow up. Early detection and treatment thus appears to have reduced collateral damage in first psychosis and altered the course and prognosis of the disorder (i.e. achieved secondary prevention). Given these empirical data it is timely to test whether *very* early intervention can actually prevent the development of disorder in individuals at high risk (i.e. primary prevention).

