### Power calculation

There are no previous studies giving any clear suggestion of the number of high-risk individuals that can be recruited from a well-defined catchment area sample like the current, but previous studies in Melbourne indicate that around 20% of first episode patients have been in contact with the PACE clinic ([name], personal communication). Studies up to now give a conservative estimate of a 20% transition rate over the first two years for a non-treated high-risk sample and subsequently a 10% risk in the active treatment group. A power analysis has shown that in order to give an achieved significant reduction of transition rates in the study population with the proposed sample size for the two groups of a) 750 000 with predicted annually detection of 150 first-episode psychosis (FEP) (Bergen and Østfold) and b) 440 000 with annually predicted reduction to 90 FEP (Stavanger and Fonna) through prodromal detection and intervention, the study will have power of 88.9% to yield a statistically significant result.

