### The psychosis incidence study

The main outcome of the intervention will be the incidence of psychotic disorders in the participating areas. This will be assessed using the same research diagnostic criteria; in all participating areas over all study years.

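### Incidence is compared between two programme areas and two non-randomised areas, and the stated 88.9% power neither follows from the printed counts nor allows for differences between areas

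*Protocol article*

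**What the plan says.** The abstract's Methods/Design paragraph sets a concurrent, parallel design "comparing the incidence of first episode psychotic disorders between two Norwegian catchment areas with prodromal detection and treatment (Stavanger and Fonna". Stavanger and Fonna have the programme. The comparators are "two catchment areas without a prodromal intervention program (Bergen and Østfold". The article describes no random assignment of areas.

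The section The psychosis incidence study fixes the endpoint: "The main outcome of the intervention will be the incidence of psychotic disorders in the participating areas". The same diagnostic criteria are to be applied "in all participating areas over all study years". The Background says that Bergen and Østfold are involved "for establishing a first-episode psychosis incidence registration as another part of this research initiative".

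The Power calculation section describes its basis as "with the proposed sample size for the two groups of a) 750 000", with 150 first-episode cases a year (Bergen and Østfold), against 440 000 residents with a predicted fall to 90 cases a year (Stavanger and Fonna). It states 88.9% power. It names no test, significance level, period or between-area variance. The same section gives about 20% of first-episode patients in prior contact with a high-risk clinic, and two-year conversion of 20% untreated against 10% treated.

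**The concern.** Information campaigns and detection teams act on whole catchment areas, so the intervention has four units, two on each side. If the areas would have differed in incidence without the programme, a comparison of levels counts that difference as programme effect, in either direction. Treating residents as the sample size ignores this source of variation: the test rejects too often when there is no effect, and the interval is too narrow.

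Much rests on the result. The abstract's Discussion would read a positive result as potentially transforming therapy, and a negative one as a sign that psychosis risk is settled early in life. A contrast of four chosen areas with an unsupported power figure carries neither conclusion.

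**Working it through.** **Inputs.** From the Power calculation section: 750 000 residents and 150 cases a year; 440 000 residents and 90 cases a year; reach 20%; conversion 20% against 10%; power 88.9%. From the inclusion dates, March 2012 to December 2016: 58/12 = 4.83 years. Assumed: alpha 0.05 two-sided; between-area coefficient of variation (CV) of 5%, 10% or 20%, which the article does not give.

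**1. The plan's own figure.**
- Rates: 150/750 000 = 20.0 and 90/440 000 = 20.45 per 100 000. At the comparison rate, 440 000 residents would yield 88 cases, so 90 is no reduction.
- Two-proportion z test, one year, per 100 000: difference 0.455, SE 2.697 under the null and 2.704 under the alternative. Power = Φ((0.455 − 1.96 × 2.697)/2.704) = Φ(−1.79) = 3.7%.
- Five years: Φ((0.455 − 1.96 × 1.206)/1.209) = Φ(−1.58) = 5.7%.
- Both count rejection in the direction of the printed difference, which is a higher rate in the programme areas.
- The stated figure returns with inputs that are not printed. With 54 cases in 440 000 (12.27 per 100 000, a 39% reduction from 88), power = Φ((7.727 − 1.96 × 2.486)/2.336) = Φ(1.22) = 88.9%.

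**2. The effect the section implies.** If 20% of future cases are reached and their conversion is halved, incidence falls by 0.20 × 0.50 = 10%, a rate ratio of 0.90 with |log| = 0.105.

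**3. Person-level power for that effect over 4.83 years.** Expected cases: 150 × 4.83 = 724.5 in the comparison areas; in the programme areas 88 × 4.83 = 425 without effect and 382.5 with it.
- SE of the log rate ratio under no effect: √(1/724.5 + 1/425) = 0.061.
- SE under a 10% reduction: √(1/724.5 + 1/382.5) = 0.063.
- Power ≈ Φ(0.105/0.063 − 1.96) = 38%.

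**4. Adding between-area variation.** With two areas on each side, the contrast gains variance CV²/2 + CV²/2 = CV² (areas of equal size assumed).
- True error of the nominal 5% person-level test: 2[1 − Φ(1.96 × 0.061/√(0.061² + CV²))].
- Power when the test's SE includes that variance: SE = √(0.063² + CV²).

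| CV (assumed) | True error of nominal 5% test | Power, 10% reduction |
|---|---|---|
| 0 | 5% | 38% |
| 5% | 13% | 26% |
| 10% | 31% | 14% |
| 20% | 57% | 8% |

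The power column treats the CV as known. If it is estimated from the four areas (t test, 2 df), power at the three non-zero CVs is 13%, 9% and 6%.

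**5. Difference in change.** With five earlier years (750 and 440 cases at the same rates), SE = √(1/750 + 1/440 + 1/724.5 + 1/382.5) = 0.087. Power for a 10% reduction = 23%. This SE contains no area-by-period variation, so it is a lower bound and the power an upper bound.

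**The case against.** Several objections have force.

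- **Baseline rates.** The article is condensed, and the words on study years sit in a sentence about uniform diagnostic criteria. A reader might infer that no pre-programme rates exist or will be used. The article does not establish that; it only describes none.
- **Power method.** No method is named, and the printed counts do not reproduce 88.9% at person level. That the calculation treated 1.19 million residents as independent is an inference from populations being called the sample size.
- **Size of the area variation.** The Rationale cites incidence "varying between 15 in the TIPS study" up to 30 per 100 000. A reader might take this as evidence of large differences among these four areas. It comes from different sources and may reflect case definition, age range and setting, so it does not support any particular CV here.
- **What drives the loss of power.** It is tempting to blame the whole gap below 88.9% on area clustering. With no area variation at all, power for a 10% reduction is already only 38%, so most of the gap is effect size.
- **Declared design.** The article openly presents a health-service, proof-of-concept study. That makes the design legitimate. It does not make the stated power a property of it.
- **Baseline adjustment is no cure.** A Poisson model with an intercept per area still treats residents as independent, and its power is lower. A permutation test on four areas cannot reach a two-sided p below 2/6 = 0.33, on levels or on changes.

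What remains is the non-randomised two-against-two contrast, the power statement with no area term, and printed counts that contain no effect.

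**Conclusion.** The point holds in this form. As described, the main comparison confounds stable area differences with the programme effect, and 88.9% is not supported by the section that states it. The arithmetic on the printed rates needs only the assumed 5% level. The 38% also assumes that the cited 20% reach and the halved conversion carry over to these areas. The error rates of 13%, 31% and 57%, and the powers of 26%, 14% and 8%, hold only at the assumed CVs and show sensitivity; they do not estimate what will happen in these four areas. The documents do not show that a baseline is unavailable, nor that an independence-based calculation was knowingly used.

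**What to change.** 1. In the Power calculation section, correct the case counts or rates so that they express the intended reduction. Restate the power with effect size, period, test, significance level and a range of between-area variance.
2. State in the design and incidence sections that this is a non-randomised comparison of four areas, and limit the conclusions in the abstract's Discussion, positive and negative, to match.
3. Where counts before March 2012 can be extracted for all four areas under one case rule applied to both periods, report the difference in change beside the level comparison, with an allowance for area-by-period variation. Comparability needs checking, because study caseness rests on research interviews and the incidence criteria require consent.
4. Do not use the first study year as baseline. Campaigns and detection teams may already alter case-finding in the programme areas, which could raise their baseline and create an apparent later fall.

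Items 1 and 2 cost only rewriting. Item 3 costs record extraction and precision: the SE rises from 0.063 to at least 0.087, and power for a 10% reduction falls from 38% to at most about 23%. That loss should be stated. No extra patients are needed.

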**Discussion:**

Positive results could potentially revolutionize therapy by treating risk earlier rather than disorder later and could open a new era of early detection and intervention in psychosis. Negative results will suggest that the potential for psychosis is determined early in life and that research should focus more on genetically linked neurodevelopmental processes.

If we can identify people about to become psychotic with high accuracy, we can track them to understand more about how psychosis unfolds. Appropriate intervention at this stage could also prevent or delay the onset of psychosis and/or subsequent deterioration, i.e., social and instrumental disability, suicide, aggressive behavior, affective- and cognitive deficits.

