### Aims

The primary aim of the current study is to test the effect of a Prodromal Detection and Treatment program at the health care systems level. The study will investigate; 1) If the combination of information campaigns and detection teams modelled will help in identifying individuals at high risk of developing psychosis early, and 2) If a graded, multi-modal treatment program will reduce rates of conversion compared to the rates seen in follow-along assessments. The study will use the knowledge obtained and the treatment strategies developed from recent experimental studies, and test them out on the health care system level as a proof-of-concept study that intervention in the prodromal phase may lead to a reduction in the development of new cases. The endpoint or main outcome will be the rate of conversion to psychosis. The study will be conducted within a translational approach, comprising clinical and genetic sub-projects as well as an FMRI sub study at Stavanger University hospital, Norway done in close collaboration with health regions in Southern Norway. The aim of these sub-projects is to identify neurobiological indicators of psychosis vulnerability.

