## Discussion

Evidence has been accumulating that it may be possible to achieve prevention in psychotic disorders. Solid evidence has come forward from the TIPS study for tertiary and secondary prevention, providing proof of concept that prevention in psychosis is possible and might be extended to the disorder itself. Direct but preliminary evidence for primary prevention has been generated by clinical trials in Australia, Europe and the US. If we can identify people about to become psychotic with high accuracy, we can track them to understand more about how psychosis unfolds. Appropriate intervention at this stage could also prevent or delay the onset of psychosis and/or subsequent deterioration, i.e., social and instrumental disability, suicide, aggressive behavior, affective- and cognitive deficits. However, there are still major methodologically and practical challenges that need to be solved. The health services need to be able to identify and recruit persons who meet the current criteria which might be difficult because individuals in the high risk group don’t necessarily seek guidance actively. Other challenges concern the sensitivity and specificity of the current UHR criteria, which in turn reflects the heterogeneity of a psychosis high-risk state as well as the heterogeneity of the traditional mental disorders.

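### A null difference in area-level incidence cannot support the abstract's conclusion that psychosis is determined early in life

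*Protocol article*

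**What the plan says.** The Discussion paragraph of the abstract gives an unconditional reading of a null: "Negative results will suggest that the potential for psychosis is determined early in life". It adds that research should then turn towards genetically linked neurodevelopmental processes. The sentence does not define a negative result and sets no condition on reach or precision.

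The section on the psychosis incidence study states that "The main outcome of the intervention will be the incidence of psychotic disorders in the participating areas". The abstract's Methods/Design paragraph makes this a comparison of Stavanger and Fonna with Bergen and Østfold. The Aims section names a different main outcome: "The endpoint or main outcome will be the rate of conversion to psychosis".

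The Power calculation says that no earlier study clearly indicates how many high-risk people can be recruited. It then cites Melbourne experience that "around 20% of first episode patients have been in contact with the PACE clinic". It assumes a "conservative estimate of a 20% transition rate over the first two years for a non-treated high-risk sample", falling to 10% under treatment, and states 88.9% power.

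The main Discussion concedes that identifying and recruiting eligible people "might be difficult because individuals in the high risk group don’t necessarily seek guidance actively", and that the sensitivity and specificity of the high-risk criteria are unresolved. It does not connect either point to how a null result would be read.

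**The concern.** The study tests a health-system programme through its effect on the number of new cases in whole catchment areas. Between the programme and that outcome stand several links: reaching people before onset, treating them effectively, counting cases equally in all areas, and having enough cases to see a difference. A failure at any link gives a null. Only a null with all the links intact would begin to say something about whether psychosis can be prevented at the prodromal stage. Even then it would speak about this package, not about when in life the risk is fixed.

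At stake is what the trial may conclude. Read as written, it could tell the field that prodromal prevention cannot work when the programme had simply reached too few future cases.

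**Working it through.** **1. The plan's own power figure.** Control areas: 150 / 750,000 = 20.0 per 100,000 per year. Intervention areas: 90 / 440,000 = 20.45 per 100,000 per year. Ratio = 20.45 / 20.0 = 1.02, so these inputs contain no reduction. SE(log RR) = sqrt(1/150 + 1/90) = 0.133 and |log RR| = 0.0225. Two-sided 5% power on one year is Φ(0.0225/0.133 − 1.96), about 4%. The stated 88.9% is not reproduced. From 20 per 100,000, that power would need a reduction of about 39% on one year or about 19% over 4.83 years (two-sided, pooled-variance test).

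**2. Inputs for an illustration.**
- Reach 20%: the Melbourne contact share in the Power calculation, used here as an assumption because the plan gives no expected reach of its own.
- Transition halved, 20% to 10%: Power calculation.
- Control incidence 20 per 100,000: 150 / 750,000.
- Window 4.83 years: inclusion from 1 March 2012 to 31 December 2016 is 58 months.
- Two-sided 5%: assumed, since neither alpha nor sidedness is stated.
- Poisson counts, no variation between areas, full reach from the first day, no extra case-finding: assumed.

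**3. Implied effect.** 0.20 × 0.50 = 0.10, so RR = 0.90 and incidence falls from 20.0 to 18.0 per 100,000.

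**4. Precision and power.** Power = Φ(|log RR| / SE − z), with SE = sqrt(1/control cases + 1/intervention cases).
- Expected control cases: 750,000 × 4.83 × 0.00020 = 724.5.
- Expected intervention cases: 440,000 × 4.83 × 0.00018 = 382.5.
- SE = sqrt(1/724.5 + 1/382.5) = 0.0632.
- Expected 95% CI: exp(−0.105 ± 0.124) = 0.80 to 1.02.
- Power: Φ(0.105/0.0632 − 1.96) = Φ(−0.29), about 38%.

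**5. Sensitivity.**

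| Change from step 4 | Power |
|---|---|
| None (4.83 years, two-sided) | about 38% |
| One year of data | about 11% |
| One-sided 5% | about 51% |
| 6.83 years (assumed: window plus the 2-year follow-along) | about 51% |
| 30% reach (RR 0.85) | about 71% |
| 15 per 100,000 (low end in Rationale) | about 30% |
| 30 per 100,000 (high end in Rationale) | about 53% |

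Reach of about 23.5% already gives 50% power at 4.83 years, two-sided.

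**6. If the programme did nothing.** Expected intervention cases are 440,000 × 4.83 × 0.00020 = 425, and SE = sqrt(1/724.5 + 1/425) = 0.061. The expected lower confidence limit is exp(−0.120) = 0.89. The interval would lie wholly above 0.90 in only about 41% of such trials, so even a true null would often leave a 10% reduction open.

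**7. The inference itself.** Low reach, an ineffective package, and extra first episodes brought to notice by campaigns run only in the programme areas can each push the rate ratio to 1 or above whatever the precision. The step from a null to early-life determination therefore fails even where power is high.

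**The case against.** The sentence is one line of outlook in an abstract, paired with an equally broad remark about positive results. It uses a soft verb, sets no test or threshold, and is not repeated in the main Discussion, which lists recruitment and the high-risk criteria as open problems. That stands: a reader might infer that the trial has adopted a formal decision rule, and the document does not support this.

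A reader might also infer that a null is the likelier outcome under the plan's own assumptions even if treatment halves conversion. That is too strong. The plan never states a 10% reduction. The 0.90 is the product of another clinic's contact share and the assumed halving, and the plan hypothesises that campaigns and detection teams will raise contact. Alpha, sidedness and the end of incidence registration are not given, and modest changes in any of these bring power to about one half or more. Gradual build-up of reach, lag, area-level variation and extra case-finding would work the other way, so the document does not settle which outcome is likelier.

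The stated 88.9% power might seem to answer the concern, but it fails on its own inputs.

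Finally, a negative result could mean the conversion outcome named in Aims. Low reach would not explain a null among treated participants. An ineffective package or too few participants still could, so the early-life inference does not follow there either.

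**Conclusion.** The point holds as one of interpretation: a non-significant difference in area-level incidence does not support the abstract's aetiological conclusion. This rests on the design alone and needs no particular power figure.

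The numbers show that an uninformative null is a realistic prospect, not that it is the expected one. At RR 0.90, power runs from about 38% (4.83 years, two-sided) to about 51% (one-sided, or 6.83 years), and it reaches about 71% at 30% reach. These figures assume 20 per 100,000, transition halved and no area-level variation, and except for the last they take 20% reach from the Melbourne figure.

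**What to change.** Delete the early-life inference from the abstract, with the redirection of research that follows from it. In its place, state that:

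- the incidence result will be reported as a rate ratio with its 95% CI;
- an interval wholly below 1 is read as a reduction;
- an interval that includes 1 is called inconclusive unless its lower limit also lies above a prespecified smallest worthwhile reduction, which the sponsor should set and justify.

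The middle condition is needed. With the SE in step 4, an observed ratio of 0.85 has a CI of 0.75 to 0.96. A test of whether the interval excludes 0.90, used alone, would wrongly call that inconclusive.

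Read any null beside the conversion rate among participants, which the scheduled SIPS assessments already track. If linkage can be arranged, also report the share of first-episode cases in Stavanger and Fonna with earlier programme contact. Ethical approval says incidence records are depersonalised before they reach the researchers, so this tabulation would have to be planned ahead of that step and is not shown to be available at present.

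The cost is a change of wording, a less definite conclusion from a null result, and a small linkage task if the reach tabulation is included.
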